### 2.7. Outcome Measures

#### 2.7.1. Primary Outcome Measure

The primary outcome measure is gait speed, which will be assessed by the 10 m walk test. 

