### 2.4. Sample Population 

The inclusion criteria for the stroke group are as follows: (1) the first occurrence of stroke with hemiparesis within the first month as confirmed by computed tomography or magnetic resonance imaging (MRI); (2) participants must be aged between 40- to 79-years-old; (3) Brunnstrom stage 3; (4) modified Ashworth scale score ≤2; (5) medically stable and able to sit unsupported for at least 30 min; (6) able to walk 10 m with or without walking aid; (7) no severe cognitive impairment, as defined by the Mini-mental State Examination (scale score greater than 10) [38], and (8) at least five degrees of active wrist extension and ankle dorsiflexion are available. The exclusion criteria are as follows: (1) comorbidity conditions including congestive heart failure, deep vein thrombosis, and malignant progressive hypertension; (2) lower limb fracture; (3) history of mental illness or on anti-psychotic drugs. The rationale to include only participants who could sit unsupported for 30 min was due to that fact that interlimb-coordinated interventions are conducted in a seated position. The Brunnstrom stage of recovery is included as a criterion to ensure that the participants have recovered some of the motor function before participation in the intervention program. The modified Ashworth scale is to ensure that motor function is not affected by high level of muscle spasticity.

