#### 2.7.2. Secondary Outcome Measure

All outcome measures will be recorded at baseline, post-intervention, and at 3 and 6 months post-intervention. Table 1 presents a brief description of each of the secondary outcome measures that will be recorded at all participating centres. The outcome measures of the 10 m walk test, Fugl–Meyer Assessment, and Action Research Arm Test are the recommended outcome measures by expert consensus from national societies in the United States for body function and activity [39]. The Berg Balance Scale (BBS) was also reported to be a tool that is valid, reliable, and sensitive to change in post-stroke balance impairment assessments despite the potential concern of the ceiling and flooring effect [40]. The timed-up and go test (TUG) was initially developed to identify balance impairment [41] and has been reported as a reliable, valid, and easy-to-administer clinical tool that can be used to assess mobility and balance [42]. Both the BBS [43] and TUG [44] are strong fall predictors. The Instrumental Activities of Daily Living has also been reported as an international gold standard despite its limitations and biases [45].

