### 2.12. Sample Size

Sample size calculation will be based on the primary outcome measures of gait speed. An increase in gait speed of 0.16 m/s has been stated as the minimal clinically significant difference in the first 60 days of stroke occurrence [54] that correlating with a meaningful improvement in disability level post intervention. The study will consider 0.3 m/s for power calculation since other study-reported changes below this value are likely to be measurement errors [55].

The sample size was determined using the sample size calculator G*Power. The calculation model is based on the F test family, the statistical “ANOVA: Repeated measures, between factors” test and the “A priori: Compute required sample size–given alpha power, and the effect size” as the power analysis type. Power calculation was based on a mean difference of 0.3 (mean of group 1 = 0.69; mean of group 2 = 0.39) and the standard deviance of each group of 0.75 with a total sample population of 60. A total of 206 participants (103 in each group) is required to provide 95% power and an effect size of 0.2. Taking a 10% missing rate into consideration, a final sample size of 226 participants (113 in each group) was determined. 

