## 4. Safety and Adverse Event Reporting

Patients with acute stroke have a likelihood of morbidity and mortality. Procedures are in place to minimize the occurrence of adverse events. Medical doctors will assess participants to ensure safe rehabilitation participation. Medically unstable patients will not be recruited for the study. Participants will be asked to exercise according to their physical capability. Trained physiotherapists/occupational therapists who work closely with the inpatient clinical team will be onsite during the exercise sessions. Any issues raised during the exercise session will be reported to the inpatient medical team. The following safety reporting procedures are in place:Serious adverse events (SAEs) are defined as an event that incurs harm to the participants, which may or may not require medical or surgical intervention as a preventative measure to avoid the following outcomes: death, further impairment of body function, damage to a body structure, and prolonged the hospitalization period.All SAEs related to the interventions will be recorded on a SAEs event report form in accordance with the procedures of each research centre.All of the SAEs related to the interventions must be reported to the Principal Investigator within 24 h of learning of the event.SAEs that are related to the interventions will be reported to the University Clinical Trial Unit and Research Ethics Committee within 15 days of the occurrence of the SAEs. The following information will be reported to relevant parties: (1) the concerned research protocol; (2) a report on the description of the SAE and subsequent outcome; (3) a proposal of changes in response to the SAE to prevent further occurrence of SAEs

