### 4.2. Data Analysis

All statistical analyses will be performed in IBM SPSS version 21 software (SPSS Inc., Chicago, IL, USA). Descriptive statistics will be conducted to describe the sample population. The demographic characteristics and baseline results for the primary and secondary outcome measures will be analyzed using analysis of variance (ANOVA) or Chi-square test for categorical data. A mixed-effect model analysis will be adopted to compare changes in all of the outcome measures between groups at the completion of the intervention and at the 3- and 6-month follow-ups. The mixed-effect model analysis will include treatment, time, and centre as fixed effects, and the participants will be included as the random effect. Changes in the outcome measures will be adjusted for age, sex, centre, and time. The level of statistical significance will be set at *p* < 0.05. Cohen’s d will be calculated to measure the effect size of the difference for every comparison. The effect size will be interpreted as follows: 0.2—small effect size; 0.5—medium effect size; and 0.8—large effect size. Stratification analysis will be conducted to explore the potential effect difference between centres. There are no planned interim analyses or stopping rules, as the power calculation has accounted for loss to follow-up. In the event of missing data during the follow-up period, the modified intention to treat principle will be followed with the last observation carried forward method. 

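### Last observation carried forward has no exception for lost walking or death, and inability to walk 10 m has no score, so such participants can be credited with a walking speed

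*Protocol article*

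**What the plan says.** Section 2.7.1 defines the primary endpoint in one sentence: "The primary outcome measure is gait speed, which will be assessed by the 10 m walk test". It does not say what is recorded when a participant cannot complete the walk.

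Section 2.4 makes walking an entry condition: participants must be "able to walk 10 m with or without walking aid".

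Section 2.7.2 sets four measurement occasions: "All outcome measures will be recorded at baseline, post-intervention, and at 3 and 6 months post-intervention".

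Section 4.2 names the analysis: "A mixed-effect model analysis will be adopted to compare changes in all of the outcome measures between groups". For missing follow-up data it says "the modified intention to treat principle will be followed with the last observation carried forward method". No type of absent value is exempted.

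Section 4 acknowledges the risk in this population: "Patients with acute stroke have a likelihood of morbidity and mortality".

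**The concern.** Inability to walk is a result, and the worst one possible on a gait-speed endpoint. Carrying forward an earlier speed replaces that result with a value from when the participant could still walk. Because the analysis compares changes, a participant who improved over the two weeks and then lost walking would count as a lasting improvement. For a participant who has died, the carried value describes nothing at all.

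The difficulty is not peculiar to carrying values forward. A likelihood-based mixed model under missing at random would also predict a speed for someone known to be unable to walk. Changing the imputation method alone would therefore not settle it: the endpoint needs a stated value for inability.

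The silence in section 2.7.1 adds a practical risk. Each of the four centres has its own assessment team (section 2.11) and records on case report forms at the site (section 4.1). The same failed walk could be entered as zero at one centre and left blank at another.

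**Working it through.** **The plan's own figure.** Section 2.12 uses means of 0.69 and 0.39 m/s and an SD of 0.75 m/s, so f = (0.30 / 0.75) / 2 = 0.20. Its conclusion is: "A total of 206 participants (103 in each group) is required to provide 95% power and an effect size of 0.2". For a between-factor repeated-measures F test the noncentrality is f² × N × m / (1 + (m − 1) × rho). Take m = 4 from the visit schedule and rho = 0.5, which is an assumption because the article gives no correlation. Then 0.04 × 206 × 4 / 2.5 = 13.18, and power at alpha 0.05 is 0.951. The 206 is reproduced, and nothing below changes it.

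**Why a carried value is always positive.** Section 2.4 requires the ability to walk 10 m, so each participant should have a baseline speed above zero. Any last observation taken while the participant could walk is also above zero.

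**Effect on one participant (illustration).** Suppose a speed of 0.39 m/s at baseline, 0.69 m/s after the intervention, then loss of walking.
- Carried forward, the 6-month change is 0.69 − 0.39 = +0.30 m/s.
- Scored as unable, it is 0 − 0.39 = −0.39 m/s.

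The two speeds are the planning group means, borrowed for illustration.

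**Effect on the comparison.** Let q be the proportion of an arm that cannot walk or has died at a visit, and b the mean speed carried for them. Relative to a score of 0 m/s, carrying forward raises that arm's mean by q × b. The shift in the treatment difference (intervention minus control) is

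q_int × b_int − q_ctrl × b_ctrl.

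With the same carried speed in both arms this is b × (q_int − q_ctrl). The documents give neither q nor b. The rates below are assumptions, and the speeds are the planning means.

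| Difference in rates | b = 0.39 m/s | b = 0.69 m/s |
|---|---|---|
| 0 points | 0 | 0 |
| 2 points | 0.02 × 0.39 = 0.008 | 0.02 × 0.69 = 0.014 |
| 5 points | 0.05 × 0.39 = 0.020 | 0.05 × 0.69 = 0.035 |

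The sign follows the arm with more failures. With control 10% and intervention 5%, the shift is −0.020 to −0.035 m/s, against the intervention. With the rates reversed it is +0.020 to +0.035 m/s, in its favour. If those who lose walking were slower beforehand, say b = 0.20 m/s, 5 points give 0.05 × 0.20 = 0.010 m/s.

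**Equal rates, unequal speeds.** With 5% failing in each arm and carried speeds of 0.69 (intervention) and 0.39 m/s (control), the shift is 0.05 × (0.69 − 0.39) = +0.015 m/s. Equal failure rates therefore do not guarantee an unbiased comparison. The two routes can add or offset.

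**Scale.** Using unrounded shifts of 0.0078 and 0.0345 m/s:
- Against the 0.16 m/s that section 2.12 cites as clinically significant: 4.9% to 21.6%.
- Against the planned 0.3 m/s: 2.6% to 11.5%.
- Against the single-visit standard error, 0.75 × √(2/103) = 0.105 m/s: at most 0.0345 / 0.105, about one third.

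**The case against.** A reader might infer that the primary analysis treats inability to walk as missing. The article does not say so. Section 4.2 applies only to missing data, and a participant who attends but cannot complete the walk could be recorded as 0 m/s, in which case nothing is carried forward. How to score a failed test is a detail that a full protocol, assessment manual or analysis plan may hold, and none of these is shown. Section 2.11 says the assessors are specifically trained. The silence of section 2.7.1 is therefore not a defect in itself.

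The size is also open to challenge. No rate of lost walking is given, medically unstable patients are not recruited, and the article expects most recovery early after stroke. The arms have equal therapy time and differ in 20 minutes of each day's content over two weeks. With 113 per arm, a 5-point difference means five or six more failures in one arm (0.05 × 113 = 5.65). Those who lose walking may have been slower than the planning means.

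Much of this stands. It rules out a flat claim about attended but failed walks, and it makes the size conditional. It does not answer the case of a participant who has died or is too disabled to attend. There the value is absent, and the rule as written supplies a positive speed. That is a stated rule giving a wrong value, whatever the unseen documents say about failed tests.

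**Conclusion.** The point holds in conditional form. The article carries a positive speed forward for a participant who has died or cannot attend because of disability, and would do the same for a failed walk if that is coded missing. It does not establish how attended failures are coded.

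Nor does it support a direction of bias. The shift is zero when rates and carried speeds match between arms, and otherwise can favour either arm. Under assumed differences of 0 to 5 points and a common carried speed of 0.39 to 0.69 m/s, it lies between 0 and about 0.035 m/s in absolute size. Larger differences in rates, or carried speeds that also differ between arms, would widen that range. This is modest beside the sampling error of one visit, but it is systematic and avoidable. It should be corrected before the data are unblinded, so that the scoring cannot depend on the results.

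**What to change.** - In section 4.2, limit the missing-data method, whichever is used, to participants whose walking status at the visit is unknown.
- In section 2.7.1, state that a living participant known to be unable to complete the 10 m walk scores 0 m/s at that visit, and say what evidence counts as known. If the full protocol already holds such a rule, refer to it.
- Report deaths by arm and carry no speed past death. Add a sensitivity analysis scoring those visits 0 m/s. Scoring deaths is debatable, so it belongs there rather than in the primary analysis.
- Add one case-report-form item separating unable to walk, not assessed and died, used identically at all four centres.

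The cost is a few sentences and one form item, with no change to sample size or treatment. The statistical downside is a small spike at zero in the gait-speed distribution. Accepting reported inability also brings a value that was not directly measured into a performance test, which is why the evidence rule should be explicit.

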#### 2.7.2. Secondary Outcome Measure

All outcome measures will be recorded at baseline, post-intervention, and at 3 and 6 months post-intervention. Table 1 presents a brief description of each of the secondary outcome measures that will be recorded at all participating centres. The outcome measures of the 10 m walk test, Fugl–Meyer Assessment, and Action Research Arm Test are the recommended outcome measures by expert consensus from national societies in the United States for body function and activity [39]. The Berg Balance Scale (BBS) was also reported to be a tool that is valid, reliable, and sensitive to change in post-stroke balance impairment assessments despite the potential concern of the ceiling and flooring effect [40]. The timed-up and go test (TUG) was initially developed to identify balance impairment [41] and has been reported as a reliable, valid, and easy-to-administer clinical tool that can be used to assess mobility and balance [42]. Both the BBS [43] and TUG [44] are strong fall predictors. The Instrumental Activities of Daily Living has also been reported as an international gold standard despite its limitations and biases [45].

### 2.8. Event Related Potentials 

The event-related potential (ERP) waveform contingent negative variation (CNV) will be recorded by a 32-channel QuickAmp amplifier and Ag/AgCl scalp electrodes (BrainProducts, Gilching, Germany). CNV is a sustained negativity that occurs after an initial stimulus (S1) and before the imperative stimulus (S2) that requires a response [51]. It is a waveform that occurs during the preparatory period between the cue and response stimuli and is an indicator for motor task initiation [52], including hand movement and gait tasks. The electrodes will be positioned in accordance with the international 10–20 system, with the additional electrodes within the covered area. The following electrodes will be used: FP1, FP2, F7, F3, Fz, F4, F8, T7, C3, Cz, C4, T8, P7, P3, P4, P8, O1, O2, TP9, TP10, FC5, FC1, FC2, FC6, CP5, CP1, CP2, CP6, PO9, O1, O2, PO10; FCz will be used as a reference electrode, and AFz will be used as a ground electrode. Data will be recorded with a sample rate of 1000 Hz in direct current mode. Each electrode will be filled with conductive gel to maintain impedance below 5 kΩ. Alpha, beta, gamma, and theta wave oscillation will be recorded and analysed at resting state. The ERP paradigm is illustrated in Figure 2.

### 2.9. fMRI

Data acquisition of functional magnetic resonance imaging (fMRI) will follow the scanning procedure from a previous study where gait function improvement was assessed [53]. The T1-weighted data set of the entire brain will be acquired for each participant. The scan parameters for blood oxygen level-dependent (BOLD)-weighted scans are as follows: TR = 200 ms, TE = 25 ms, field of view 200 × 200, matrix 64 × 64, and a slice thickness of 3 mm. The scanning paradigm involves five active movement blocks of ankle plantar flexion. Each block is triggered by an auditory command with a 20 s epoch of rest in between each block. The scanning time of the movement of the affected ankle is 200 s (the amount of time it takes to complete five active movement blocks of ankle plantar flexion). A metronome with the beat set to 30 beats per minute will be provided to set the pace of the ankle movement. All of the participants will be given sufficient time to practice the movement task prior to data recording. Imaging data will be analysed by the software Statistical Parametric Mapping 8 implemented in MATLAB (software available at https://www.fil.ion.ucl.ac.uk/spm/, accessed on the 9 November 2021). The anatomic space template was adopted to normalize the functional scan images. The within-subject before and after intervention will be analysed by paired sample *t*-test. 

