## Abstract

Background: The efficacy of interlimb-coordinated training on gait and upper limb functional improvement remains unclear. The latest published randomized controlled trials have supported the potential benefits of interlimb-coordinated training to enhance gait function. Upper limb functional recovery may also benefit from interlimb-coordinated training since most everyday activities require the coordinated use of both hands to complete a task. This study investigates the efficacy of interlimb-coordinated training on gait and upper limb functional recovery over a short-medium term period. Methods: A total of 226 acute stroke patients will be recruited from four centres over four years. Patients will be randomly allocated to either conventional therapy or conventional therapy plus interlimb-coordinated training. Outcomes will be recorded at baseline, after 2 weeks of intervention, and at 3- and 6-months post-intervention. Gait speed is the primary outcome measure. Secondary outcome measures include Fugl–Meyer Assessment of Motor Recovery, Berg Balance Scale, Timed Up and Go test, Action Research Arm Test, electroencephalography, and magnetic resonance imaging. Conclusion: The results of this trial will provide an in-depth understanding of the efficacy of early interlimb-coordinated intervention on gait and upper functional rehabilitation and how it may relate to the neural plasticity process.

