The primary aim of the present study is to investigate the effect of interlimb-coordinated intervention on gait and motor function in patients with stroke at the acute stage. It is hypothesized that acute stroke patients who receive interlimb-coordinated intervention will significantly improve gait and upper-limb motor function. These improvements would be significantly higher than those who receive conventional therapy immediately after the 2 weeks of intervention and at the 3- and 6-month follow-up periods. The secondary aim is to investigate the neural plasticity changes that are induced by interlimb coordinated intervention after 2 weeks of intervention and at the 3- and 6-month follow-up periods. It is also hypothesized that the participants who undergo interlimb-coordinated intervention would have stronger cortical activation at rest and during gait and a shorter neural processing time to initiate a motor task than the participants in the control group immediately after intervention and at the 3- and 6-month follow-up periods. 

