The key principle of motor function recovery post stroke is neural plasticity. A previous study indicated that function improvement is related to cortical reorganization post-intervention [53]. However, the optimal strategy for intervention application in order to increase cortical activation and motor skill learning has yet to be determined [27]. Early literature indicated that the activation patterns related to bimanual task performance were not similar to unimanual tasks such as finger opposition [63]. Recent literature propagates the theory that unimanual motor tasks involve bi-hemispheric activation patterns that are similar to the bilateral neural activation that is typically observed during bimanual movements [64]. This theory is given further support by a study that reported bimanual coupling effects observed during affected and unaffected hand tasks in an individual with stroke [65]. Another study utilized fMRI to compare the inter-regional connectivity and inter-regional activation between the bimanual in-phase and bimanual antiphase upper limb task in healthy individuals. Significant activation of the supplementary motor area, cerebellum, thalamus, and the cingulate motor area were observed during the bimanual antiphase task but not during in-phase movement [66]. The connectivity analysis also indicated stronger neural coupling during antiphase movement than during bilateral in phase and unimanual movement. Antiphase movement is similar to gait and requires the precise spatial and temporal control of the limbs. Spatial and temporal control is also required during single-hand movement due to the inhibition of the ipsilateral motor area, as evidenced by the presence of neural activity in the bilateral motor cortex [67]. It is anticipated that the interlimb-coordinated intervention that is provided at the acute stage will provide higher inter-regional connectivity and cortical activation when compared to conventional therapy, providing further evidence to support the regime to improve motor function in patients with stroke. In conclusion, this proposed research is set to provide information on the interlimb coordinated intervention as an early intervention program for patients with stroke. 

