**Figure 3 brainsci-11-01495-f003:**
[figure not shown]
Bicycle ergometer for interlimb coordinated intervention.

**Table 1 brainsci-11-01495-t001:** A brief description of each of the secondary outcome measure that will be recorded at all participating centres.

Fugl-Meyer Assessment of Motor Recovery (FMA) [46]	It is a validated tool to evaluate motor function, balance, and joint function in stroke-related hemiplegic patients. The interpretation of FMA is as follows: <50 = Severe; 50–84 = Marked, 85–94 = Moderate; 95–99 = Slight.
Berg Balance scale (BBS) [47]	The BBS consists of 14 balance-related tasks that include sit to stand, stand to sit, and standing on one foot. It was developed to assess the ability to maintain dynamic and static balance.
Timed up and go test (TUG)	The test requires the person to rise from a chair and walk 3 m at a comfortable pace, turn around at the 3 m mark, and walk back to the starting point. The test’s score is the time it takes the person to complete the test. A cut off of 14 s was proposed to be “normal” [48].
Action Research Arm Test (ARAT) [49]	ARAT is a 19-item test that is divided into four sub-tests, which consist of grasp, grip, pinch, and gross arm movement. A score of between 0 to 4 is given to each task: 0—can perform none of the test; 1—performs part of the test; 2—takes abnormally long or has great difficulty in completing the test; 3—able to perform the test normally.
Instrumental Activities of Daily Living (IADL) [50]	The IADL [26] is a functional disability scale that assesses the functional level by asking whether a person receives personal help with daily living activities, such as using the telephone, getting to places outside the house, grocery shopping, preparing meals, doing housework or handyman work, laundry, taking medications, and managing finances.
Electroencephalography (EEG)/Event related potential (ERP)	Parameters of contingent negative variation (CNV), alpha, beta, gamma, and theta wave oscillation.
Functional magnetic resonance imaging (fMRI)	The voxel count T1-weighted data set of the entire brain will be acquired for each participant. The scan parameters for blood oxygen level-dependent weighted scans are as follows: TR = 200 ms, TE = 25 ms, field of view 200 × 200, matrix 64 × 64, and a slice thickness of 3 mm.

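### The fMRI section names a within-subject paired t-test that cannot compare the arms, and the article does not reconcile it with the between-group mixed model promised for all outcomes

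*Protocol article*

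**What the plan says.** - **Section 2.9 (fMRI).** Imaging data are analysed in SPM8. The one test named is: "The within-subject before and after intervention will be analysed by paired sample" t-test. No group term and no follow-up scan is mentioned.
- **Section 4.2 (Data Analysis).** "A mixed-effect model analysis will be adopted to compare changes in all of the outcome measures between groups", at the end of the intervention and at 3 and 6 months. "The mixed-effect model analysis will include treatment, time, and centre as fixed effects, and the participants will be included as the random effect". The section places all statistical analyses in SPSS.
- **Status of fMRI.** The Abstract ends its list of secondary outcomes with "electroencephalography, and magnetic resonance imaging", and Table 1 lists fMRI among them. Section 2.7.2 and Table 2 schedule the scan at baseline, after the intervention, and at 3 and 6 months.
- **What imaging is expected to show.** The Discussion expects that the intervention "will provide higher inter-regional connectivity and cortical activation when compared to conventional therapy". The secondary hypothesis in the Introduction is likewise set against control: "stronger cortical activation at rest and during gait" and a shorter neural processing time "than the participants in the control group immediately after intervention and at the 3- and 6-month follow-up periods".

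**The concern.** The question about cortical change is comparative, but the test attached to fMRI is not. A paired test asks whether activation differs between two scans of the same people. It makes no use of the randomised control arm, whether it is run in each arm or in everyone together.

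This matters more than usual in this population. Patients enter within the first month of stroke (Section 2.4), and the Discussion says that the bulk of recovery falls in that month. Both arms receive 120 minutes of therapy a day (Table 3). Cortical change from baseline is therefore plausible in both arms even if interlimb training adds nothing. If the Section 2.9 test were reported as the fMRI result, the neuroplasticity finding would not rest on the randomisation.

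**Working it through.** **Step 1: the two sections side by side.**

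| | Section 2.9 | Section 4.2 |
|---|---|---|
| Comparison | within subject | between groups |
| Occasions | before and after | end of intervention, 3 and 6 months |
| Software | SPM8 | SPSS |
| Scope | fMRI | all outcome measures |

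The two can coexist only if the paired test is a descriptive image-level step and some fMRI summary then passes into the mixed model. The article says neither. Table 1 mentions a voxel count but does not tie it to the model. Sections 2.8 (ERP) and 2.10 (fNIRS) name no test and so fall to Section 4.2 by default. Only fMRI carries its own rule, so a reader may take that as its analysis.

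**Step 2: does Section 4.2 settle the contrast?** It lists treatment, time and centre and names no treatment-by-time term. If the response is change from baseline, the treatment term gives a between-group difference in change averaged over follow-ups. If the response is the raw value at all occasions, the difference in change sits in the interaction. In both cases, separate comparisons at each of the three follow-ups need the interaction.

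**Step 3: size of the problem (illustration).** The plan states no effect size, variance, power or sample size for fMRI, so there is no fMRI figure to reproduce. The inputs are:

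- n = 103 per arm: the Section 2.12 figure for gait speed before dropout, assumed here to apply to fMRI.
- Significance level 0.05 (Section 4.2), taken as two-sided, for a single activation summary.
- True treatment effect zero.
- Common mean change d in both arms, in SDs of the change score: not in the documents, assumed to be 0.1 to 0.5.

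For the paired t-test in the intervention arm, the statistic follows a noncentral t distribution with n − 1 = 102 degrees of freedom and noncentrality d√n, where √103 = 10.15. The chance of significance is the probability that it exceeds the two-sided 5% critical value in absolute size.

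For a two-sample test of change, the expected difference is d − d = 0 whatever d is, so the error rate should stay at 5%. A simulation of 20,000 trials per value checks this.

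| d | Noncentrality | Paired test, intervention arm | Between-group test of change |
|---|---|---|---|
| 0.1 | 1.01 | 17% | not simulated |
| 0.2 | 2.03 | 52% | 5.1% |
| 0.3 | 3.04 | 85% | 4.8% |
| 0.5 | 5.07 | 99.9% | 5.2% |

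The paired test is correctly detecting a change over time. That change says nothing about interlimb training.

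**The case against.** The strongest reply is that Section 4.2 already covers fMRI. It applies a between-group model to every outcome measure at every follow-up, and fMRI is one of those outcomes. Section 2.9 does not say that its paired test replaces that model or supports a treatment claim. The test follows the image normalisation step and may be meant only to describe change within patients. An article also condenses, and second-level SPM detail often sits in a fuller document.

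Much of this stands, and it rules out several stronger readings that a reader might infer:

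- *That fMRI has no between-group analysis, or that only two of the four scans are used.* The wording of Section 4.2 contradicts both.
- *That the trial will claim an effect when one arm is significant and the other is not.* Under equal true change that rule would disagree between arms with probability 2p(1 − p), which is 50% at power p = 0.5 and 32% at p = 0.8. The article states no such rule and no power for fMRI, so these figures do not measure a flaw in this plan.
- *That the plan mistakes recovery for a training effect.* Section 2.9 names a test and draws no causal conclusion from it.
- *That the Introduction's activation hypothesis is specifically about fMRI.* It refers to rest and gait, which resting EEG and fNIRS measure, while the fMRI task is ankle plantar flexion. The comparative expectation for fMRI rests mainly on the Discussion.

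The reply does not remove the mismatch in the current text. The specific section names a test that cannot address the comparative question, the general section promises one that can, and nothing says which governs or how SPM8 output reaches the SPSS model. This is an unreconciled statement, so the condensed format does not excuse it.

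**Conclusion.** The point holds as a failure to reconcile Sections 2.9 and 4.2. The paired t-test is the only image-level fMRI analysis named, and it cannot test a difference from conventional therapy. The between-group model in Section 4.2 covers fMRI on its wording but is not linked to any fMRI quantity.

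The 52% to 99.9% against about 5% shows what would follow if the paired test in the intervention arm were read as evidence of a treatment effect. It is not an estimate of this trial's error rate: it rests on the assumed common change of 0.2 to 0.5 SD and on 103 scanned patients per arm. At 0.1 SD the paired figure is 17%. The conclusion that a paired test cannot separate training from recovery needs none of these assumptions.

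A secondary outcome is affected, and the gait-speed analysis is untouched. The text should still be corrected before analysis, because fMRI is one of the measures meant to carry the neuroplasticity conclusion.

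**What to change.** Amend Section 2.9 to state that:

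1. treatment inference on fMRI comes from the between-group comparison of change, either as group × time in the SPM second-level model or as a two-sample test on individual change maps;
2. region-level activation summaries, named in advance, are analysed in the Section 4.2 mixed model with a treatment-by-time term, using all scheduled scans;
3. paired t-tests are descriptive only.

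Name the treatment-by-time term in Section 4.2 as well, so that the two sections agree.

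The cost is analysis wording only. The scans are already scheduled in both arms at all four occasions, so no extra patients, visits or imaging are needed.
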